## 4 Study goals

### Primary endpoints:

- Percentage of eligible couples who will accept to participate to the TREAT-panel (Cohort TREAT panel)
- Percentage of eligible couples who will accept to participate to the TREAT-panel in silico with WGS backbone (Cohort TREAT-WGS)
- Percentage of study participants in whom a pathogenic or likely pathogenic variant in appropriate inheritance model will be identified through TREAT-panel
- Percentage of study participants in whom a pathogenic or likely pathogenic variant in appropriate inheritance model will be identified through TREAT- WGS
- Percentage of study participants resulted fully negative at the gNBS (through both TREAT-panel and TREAT- WGS)

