### 5.2 Inclusion and exclusion criteria

#### Inclusion criteria:

- Newborns born in one of the participating hospitals
- Informed consent signed by both parents/legal guardian to participate in TREAT-panel
- Informed consent signed by both parents/legal guardian to participate in TREAT- WGS

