#### Exclusion criteria:

- Lack of the above criteria

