**Important Note:**

The couples' choice to participate to the two different cohorts' studies (TREAT-panel and TREAT-WGS) will be free, recruitment will be competitive in both cohorts, meaning that when reached the established number of infants to be screened (200 for TREAT-WGS, and 18.000 for the TREAT panel) the recruitment will be closed for both cohorts.

A schematic representation of gNBS pipeline is reported in **Appendix IV**.

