### 9.4 Data collection

Data collection and data management will be conducted in compliance with the principles of the Declaration of Helsinki (1996), with the principles of Good Clinical Practice (GCP), with the GDPR (General Data Protection Regulation) as well as with national data protection regulation of participating countries.

For the participation in the study the following data are recorded: gender, name, date of birth, blood sample, inclusion and exclusion criteria.

Possible disease-relevant data such as gender, age, phenotypic characteristics and date of examination, as well as diagnosis of genetic analysis, confirmation of diagnosis and therapy will be collected and shared in the database.

All raw data, such as patient files, are source documents. Their availability is ensured for routine monitoring. The participation of the individual participant in the study is documented. The study leader maintains an independent list for the identification of the study participant. This list contains the names and date of birth as well as pseudonymisation codes of the participants. The study leader is responsible for the quality of data collection and storage. All data will be collected in the following repositories:

- Birth/clinical centers Hospital certified (ITC) repositories
- CNAG and GENOOX datasets
- S4C cloud

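### Two primary endpoints measure acceptance among eligible couples, but the only eligibility criteria already require signed consent, and no count of couples offered or declining is described

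*Protocol*

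**What the plan says.** Section 4 lists five primary endpoints. Two are acceptance rates: "Percentage of eligible couples who will accept to participate to the TREAT-panel (Cohort TREAT panel") and "Percentage of eligible couples who will accept to participate to the TREAT-panel in silico with WGS backbone (Cohort TREAT-WGS").

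The protocol does not define eligibility for couples. Section 5.2 gives three inclusion criteria for newborns: "Newborns born in one of the participating hospitals", "Informed consent signed by both parents/legal guardian to participate in TREAT-panel" and "Informed consent signed by both parents/legal guardian to participate in TREAT- WGS". The one exclusion criterion is "Lack of the above criteria".

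Four other places bear on the denominator:

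- **Section 5.1** allows the study to be offered to all parents or guardians of a newborn at participating hospitals and related birth centres. It treats consent to one cohort or the other as the condition for enrolment.
- **Section 5.3** informs couples at one or more of three checkpoints. Its Important Note gives them a free choice of cohort and sets targets of 18,000 (panel) and 200 (WGS). It adds that, once the set number is reached, "the recruitment will be closed for both cohorts".
- **Section 9.4** says: "For the participation in the study the following data are recorded: gender, name, date of birth, blood sample, inclusion and exclusion criteria".
- **Section 4 (secondary endpoints) and Section 8** plan to use the accept or decline decision when WGS is proposed, and to examine differences in acceptance between countries.

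**The concern.** An acceptance rate needs a denominator that includes couples who said no. Under the Section 5.2 criteria a couple that declines is not eligible, so it leaves the denominator as well as the numerator. The rate then carries no information about uptake.

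Whether gNBS is acceptable to parents is one of the main questions of the study. The country comparison and the secondary endpoint on WGS compliance need the same denominator. If it is chosen after the data are in, the choice could set the headline figure. If refusals were not counted at the sites during recruitment, no later analysis plan can recover them.

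Two further points affect the same endpoints. The two consent criteria are listed without 'or', although an infant joins one cohort. The WGS endpoint does not limit its couples to Italy, where the sub-study runs (Section 1), or to the time when WGS places were open.

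**Working it through.** The protocol states no expected acceptance rate, so there is no planned figure to reproduce. The check is of the definition first, then of how far the result depends on the denominator. One infant per couple is assumed throughout.

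**1. Section 5.2 reading.** Acceptance = accepting couples / eligible couples. Every eligible couple has signed, so:

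- Panel: 18,000/18,000 = 100%.
- WGS: 200/200 = 100%.

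**2. Couples offered as denominator.** Inputs are the targets in Section 5.3 and an assumed uptake p of 30% to 90%. Couples offered = N/p; decliners = N/p − N; 95% half-width = 1.96 × √(p(1 − p)/offered).

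| Assumed p | Panel offered | Panel decliners | Half-width (points) | WGS offered | WGS decliners | Half-width (points) |
|---|---|---|---|---|---|---|
| 30% | 60,000 | 42,000 | 0.37 | 667 | 467 | 3.48 |
| 50% | 36,000 | 18,000 | 0.52 | 400 | 200 | 4.90 |
| 70% | 25,714 | 7,714 | 0.56 | 286 | 86 | 5.31 |
| 90% | 20,000 | 2,000 | 0.42 | 222 | 22 | 3.94 |

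The same enrolled numbers fit any of these rows. Sampling error is small, especially for the panel, so the denominator decides the answer.

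**3. Effect of cohort choice on the panel rate.** A couple choosing WGS counts as not accepting the panel unless a rule says otherwise. Assume 70% accept some form of gNBS.

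- All countries: offered = (18,000 + 200)/0.70 = 26,000. Panel rate = 18,000/26,000 = 69.2%, which is 0.8 points below 70%.
- Italy only, taking the 14,000 infants in Section 10.6 as panel infants: offered = (14,000 + 200)/0.70 = 20,286. Panel rate = 14,000/20,286 = 69.0%, which is 1.0 point below.

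**4. Effect of the cap on the WGS rate.** The numerator is fixed at 200, and the denominator depends on who is counted.

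| Couples counted | WGS rate |
|---|---|
| 1,000 seen while WGS was open (assumed) | 200/1,000 = 20% |
| 2,000, if counting goes on after the places are filled (assumed) | 200/2,000 = 10% |
| All Italian couples from step 3 | 200/20,286 = 1.0% |
| All couples in six countries from step 3 | 200/26,000 = 0.8% |

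The last three rows apply only if panel recruitment goes on after the 200 WGS places are filled, which Section 5.3 leaves unclear.

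**The case against.** The best defence is that the intended meaning is plain. Section 5.2 sets enrolment criteria for newborns, while the endpoints count couples, and listing consent among inclusion criteria is common. An endpoint about eligible couples who accept makes sense only if some can decline, and Section 5.1 names the natural population. The analysis is mainly descriptive, no test or threshold hangs on acceptance, and details of denominators often go into an analysis plan, which is not shown here.

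Much of this stands. Section 5.1 is a workable denominator and shows that the endpoints can be rescued. But it only permits an offer; it does not define eligible, and the endpoints do not point to it. An analysis plan can choose a definition, but it cannot supply refusals that were never tallied.

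Four stronger readings are tempting, and the documents do not support them:

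- *Couples must consent to both cohorts.* The bare list in Section 5.2 reads that way, but Section 5.1 says one or the other and Section 5.3 describes a free choice. This is a drafting slip, and the circularity does not depend on it.
- *Decliners are never recorded.* The protocol does not say so. Section 9.4 lists data for participants and does not rule out an aggregate tally. The secondary endpoint and Section 8 presuppose that declines are known. The attached data management deliverables, which are not available here, may describe a log.
- *Choice of WGS seriously distorts panel acceptance.* With 200 WGS places against 18,000, the shift is about 1 point.
- *Reaching 200 closes WGS alone.* The Important Note can also be read as closing both cohorts together, in which case no later couples would dilute the WGS rate.

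**Conclusion.** The concern holds as a defect of definition in two of the five primary endpoints. The other three count study participants and are not affected. Acceptance is 100% by construction if eligible takes its meaning from Section 5.2, the only criteria given. It becomes informative only with a denominator that the protocol does not link to the endpoints and describes no means of counting.

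The size of the problem depends on the true uptake, which the documents do not give. Over an assumed 30% to 90%, the panel's 18,000 acceptors stand for 60,000 down to 20,000 offers. The WGS rate is the more fragile of the two: it depends on the period and the country counted. The matter needs settling before recruitment, because the missing quantity is a count made at the sites.

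**What to change.** 1. **Section 4.** Define the denominator for each cohort as all couples at participating sites who were offered that cohort while it was open. Count each couple once, at its final decision, and do not make the definition conditional on consent. For WGS this limits the count to Italy and to the open period.
2. **Section 4.** Report acceptance of any gNBS, and the choice of WGS or panel among couples offered both.
3. **Section 5.2.** Put 'or' between the two consent criteria.
4. **Section 5.3.** Clarify whether reaching 200 closes TREAT-WGS alone or both cohorts. Either reading can be made to work, but the denominator needs one of them.
5. **Sites.** Keep an anonymous aggregate tally of couples offered, accepting and declining, by cohort. If the data management deliverables already provide for this, a cross-reference is enough.

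The cost is wording in three sections and a small tally burden at each site. No personal data on couples who decline are needed.

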### Secondary endpoints:

- Clinical and therapeutic follow-up of infants with positive findings in gNBS (through ERN collaboration and guidelines)
- Carrier frequency of recessive diseases (both autosomal and X-linked) and percentage of variants of unknown significance identified through gNBS (through both TREAT-panel and TREAT-WGS)
- Percentage of infants resulted positive at the gNBS TREAT-panel (through TREAT-panel and TREAT-WGS) who got access to the approved existing approved treatments
- Technical assessment of the TREAT-WGS
- Comparison of feasibility and detection rate (TREAT-panel vs TREAT-WGS )

- Comparison of gene coverage (TREAT-panel vs TREAT-WGS)
- Evaluation of number and type of reported variants (TREAT-panel vs TREAT WGS)
- Assessment of couples/expecting parents' compliance to a WGS screening test (assessed through parents' decision to accept/decline the TREAT-panel when WGS as testing method is proposed)

**Please note:** All infants with positive findings at gNBS (through both TREAT-panel and TREAT-WGS) will be addressed into the standard of care procedures at the ERN excellence center for diagnosis and treatment. **Appendix III** shows the list of ERNs in which University Hospital of Ferrara and OPBG (Italian S4C centers) are Health Care Providers and representatives.

## 5 Study population

### 5.1 General

Participation in the study can be offered to all parents and/or legal guardians of a newborn at participating hospitals and related birth centers. It is planned to include 18.000 newborns. Only couples with signed consent are allowed to participate in the study. Both parents must sign the informed consent to get their infant enrolled in the TREAT-panel study or in the TREAT- WGS .

### 5.2 Inclusion and exclusion criteria

#### Inclusion criteria:

- Newborns born in one of the participating hospitals
- Informed consent signed by both parents/legal guardian to participate in TREAT-panel
- Informed consent signed by both parents/legal guardian to participate in TREAT- WGS

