### 5.3 Recruiting

Recruitment of research participants will be performed using the process already adopted for the metabolic newborn screening programs in participating countries. In Italy, this includes 48 rare diseases and is well established in all Regions, although with some differences. Following the already existing NBS pipeline will ensure to address and recruit a representative sample without neglecting any minority meeting the concepts of equality and equity also in relation to the well-known heterogenous ethnic

composition of European population due to the important immigration phenomenon which is ongoing in all Member States.

The recruitment will be competitive and will last at least 12 months (with the possibility of extension to reach the enrolment target).

In detail, the information to the parents will be carried out through dedicated videos, flyers/leaflets, and meetings during one or more pregnancy checkpoints (CKPTs): an early CKPT in the first half of pregnancy, a major checkpoint at the end of pregnancy and a rescue checkpoint just after birth at DBS collection for biochemical NBS.

The administration of dedicated videos at the various CKPTs will take place always in the presence of healthcare personnel (gynaecologist/midwife/neonatologist/geneticist). The dedicated videos will also be available online -S4C website (<https://screen4care.eu/>)- should the couple wish to review them later; moreover, it will be possible to make requests for further clarification since the dedicated project' email address [[contact]](mailto:[contact]) is available. Furthermore, on the S4C website will be published a poster describing the procedure and a section dedicated to FAQs ("*Frequently asked questions*") is also planned.

If parents give consent to project' participation, a project dedicated DBS card reporting the S4C logo (S4C-DBS) will distributed at S4C birth centers to collect blood samples from enrolled neonates and then shipped to the S4C sequencing Hub (OPBG, Rome Italy) where all European samples, will be sequenced.

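### Two primary endpoints measure acceptance among eligible couples, but eligibility itself requires signed consent, and the protocol does not say where offers and refusals are recorded

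*Protocol*

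**What the plan says.** **Endpoints.** The first primary endpoint in section 4 of the protocol is the "Percentage of eligible couples who will accept to participate to the TREAT-panel (Cohort TREAT panel". The second is the "Percentage of eligible couples who will accept to participate to the TREAT-panel in silico with WGS backbone (Cohort TREAT-WGS". A secondary endpoint judges compliance with WGS from parents' decisions to accept or decline, and section 8 plans to compare acceptance between countries.

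**Eligibility.** Section 5.2 holds the only list of criteria. One concerns place of birth: "Newborns born in one of the participating hospitals". The others are consents: "Informed consent signed by both parents/legal guardian to participate in TREAT-panel", and a parallel line for TREAT-WGS. The sole exclusion criterion is "Lack of the above criteria".

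**Offer.** Section 5.1 is wider: "Participation in the study can be offered to all parents and/or legal guardians of a newborn at participating hospitals and related birth centers". It asks for both parents' signatures for one cohort or the other. Section 5.3 has couples informed at one or more of three points: "an early CKPT in the first half of pregnancy, a major checkpoint at the end of pregnancy and a rescue checkpoint just after birth". Couples choose freely between the cohorts, and recruitment closes at 18,000 for the panel and 200 for TREAT-WGS.

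**Data.** Section 9.4 states: "For the participation in the study the following data are recorded: gender, name, date of birth, blood sample, inclusion and exclusion criteria". Section 9.2 covers storage of signed consents. Section 9.7 describes the data kept for two groups of screened infants, those without and those with pathological findings.

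**The concern.** An acceptance percentage needs a denominator that includes those who said no. Section 5.2 defines eligibility so that a refusal makes a couple ineligible, and the sections on data do not mention the refusals or the offers. If sites follow the protocol as written, the endpoint is either circular or lacks its denominator.

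Two of the five primary endpoints are at stake, together with the secondary endpoint on WGS compliance and the country comparison of acceptance. An analysis plan written later can choose a denominator, but it cannot supply counts that sites did not take. The three primary endpoints on genetic findings among participants are not affected.

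**Working it through.** The protocol states no expected acceptance rate, number to be approached or precision, so there is no figure to reproduce. The check is to apply its definitions.

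**1. Literal reading.** Acceptance = consenting couples / eligible couples. Under 5.2, eligible means born in a participating hospital and consented. Numerator and denominator are then the same set:
- TREAT-panel: 18,000 / 18,000 = 100%
- TREAT-WGS: 200 / 200 = 100%

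**2. Intended reading.** Section 5.1 speaks of an offer to all parents at the sites, and the secondary endpoint on WGS speaks of declining. Together they point to acceptance = couples who signed / couples offered. No section ties the term eligible to that population.

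**3. Is that denominator collected?**

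| Section | What it provides for | Offers or refusals? |
|---|---|---|
| 9.2 | Signed consents | Not mentioned |
| 9.4 | Items recorded for participation | Not mentioned |
| 9.7 | Data on screened infants | Not mentioned |

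**4. How much the missing count matters.** Take the enrolment targets as numerators, one newborn per couple for simplicity, and assumed numbers offered, M. Then acceptance a = N/M, and the 95% half-width is 1.96 × √(a(1−a)/M).

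| Cohort (N) | Assumed offered M | Acceptance | Not accepting | Half-width (points) |
|---|---|---|---|---|
| Panel (18,000) | 20,000 | 90% | 2,000 | 0.4 |
| Panel (18,000) | 30,000 | 60% | 12,000 | 0.6 |
| Panel (18,000) | 60,000 | 30% | 42,000 | 0.4 |
| WGS (200) | 250 | 80% | 50 | 5.0 |
| WGS (200) | 400 | 50% | 200 | 4.9 |
| WGS (200) | 1,000 | 20% | 800 | 2.5 |

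These values of M say nothing about the true rate. They show that, with the numerator fixed by the recruitment target, the answer rests on M. Sampling error would be under one point for the panel and about five points or less for TREAT-WGS, whereas the choice of M moves the result by tens of points.

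**5. Other gaps in the denominator.**
- Section 5.1 includes related birth centers; 5.2 names participating hospitals only.
- Section 5.1 allows consent to either cohort; 5.2 lists both consents with no alternative between them.
- Information may start in the first half of pregnancy, before the place of birth is known, and no rule says which decision counts.
- TREAT-WGS is planned in Italy only, with free choice between cohorts. Whether a couple offered both that takes the panel counts as a WGS refusal is not stated.

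**6. What could be recovered later.** Recruitment follows the national newborn screening process (5.3), and national screening is required alongside the study (section 7, on medical defensiveness). Births per centre should therefore be obtainable afterwards. Births do not separate couples who declined from couples who were never asked.

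**The case against.** The strongest reply is that nobody would report 18,000/18,000. Listing consent among the inclusion criteria is ordinary drafting, the endpoint itself presupposes that some eligible couples decline, and sections 4 and 5.1 make the intent plain. The analysis is mainly descriptive, and exact denominators are often left to the analysis plan. Data management deliverables are attached to the protocol but not shown, section 9.7 says that one of them describes the screening pipelines in more detail, and the pipeline figure is missing here.

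Much of this stands. The intent is clear, and a log may be described elsewhere. What does not fall away is that the protocol's only definition of eligibility contradicts its lead endpoint, and that the counts must be taken during recruitment.

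A reader might infer more than the documents support:
- *That nobody keeps the count.* The text shown is silent on this; it does not say that refusals go unrecorded.
- *That three checkpoints inflate the denominator threefold.* The endpoint is a percentage of couples, and the checkpoints are occasions for information, so counting offers is not a reading of it.
- *That a family must sign both consents.* Section 5.1 and the free choice in 5.3 show otherwise; the list in 5.2 only needs rewording.
- *That acceptance is lost altogether without a log.* A figure based on deliveries remains plausible.

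**Conclusion.** The point holds in this form: as written, primary endpoints 1 and 2 are circular (100% by construction). On the evident intent, they need an offered-couples denominator that no section shown provides for. The contradiction between sections 4 and 5.2 is in the text and depends on no assumption. The data-collection half rests on the silence of 9.2, 9.4 and 9.7, and would reduce to a missing cross-reference if an attached deliverable contains the log.

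The size of any error cannot be given, because the protocol states no number offered; the 90%, 60% and 30% figures are illustration only. What would be lost for good is the split between declining and never being asked. This should be settled while refusals can still be logged prospectively.

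**What to change.** **Section 5.2.** Separate eligibility (birth at a participating site while recruitment there is open) from enrolment (signed consent for TREAT-panel or TREAT-WGS). Reconcile 5.1 and 5.2 on related birth centers.

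**Section 4.** Define acceptance as couples who signed divided by eligible couples offered that cohort while it was open, each couple counted once on its final decision. For TREAT-WGS, restrict the denominator to couples at Italian sites who were offered WGS. State that a couple offered both that chooses the panel counts as not accepting WGS but as accepting genetic newborn screening overall.

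**Section 9.4.** Add an anonymous tally per centre of couples offered, cohort offered, accepted and declined. If an attached deliverable already provides this, cite it instead. No identifiers of declining couples are needed.

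**Supporting figure.** Report couples who signed divided by deliveries at the centre in the same period. Deliveries are the right unit because screening cards count infants, so twins and repeat cards would distort it.

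**Cost.** A wording amendment and a small amount of record-keeping at sites. No clinical procedure changes.
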